### 2.8. Data Management

All information from the study will be input into the computerized database developed by the Guangzhou Huibo Information Technology Co., Ltd. (Guangdong, China), under the study ID and together with the grouping data. Simultaneous double inputs by two independent providers will be adopted in order to match the two copies of the datasets so as to figure out any possible data error latterly. Data inputs will be managed by an experienced statistic professor.

### 2.9. Sample Size Consideration

According to one risk factor in the prediction model, 10 to 15 positive events (UI progress) are be required. It is preliminarily estimated that there are about 10 meaningful risk factors, so 100–150 cases need to be included in the study to get enough statistical power. In consideration of this, 15–20% of the patients were lost in follow-ups [6,9], and the number of participants in the training and validation groups are at a ratio of 2:1, at least 188–282 participants in total are required in order to have statistical power. As more than the anticipated number of targeted women expressed their willing for participation, we planned to recruit 800 participants at most in order to get greater power for the study.

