## 2. Materials and Methods

### 2.1. Study Design and Setting

The study is conducted as a prospective multicenter study to collect epidemiological factors for the analysis of the impacts of physical activity, chronic diseases, pregnancy and delivery, genetic characteristics, pelvic floor function assessment (e.g., pelvic floor muscle strength, pelvic floor ultrasound, pelvic floor electrophysiology, and morphology index), and other factors in elderly women. Data analysis will be conducted by means of bioinformatics and mathematical modeling objectives to investigate the influence of UI progress and prognosis related factors, and to construct a prediction model of UI progress in elderly women. This study is carried out by Peking University People’s Hospital in Beijing, in cooperation with Wuhan University People’s Hospital in Wuhan, China. A total of 800 patients will be recruited, 400 from Beijing and 400 from Wuhan. Four district-level hospitals in Beijing are involved as the sub-centers in Beijing, namely Tongzhou District Maternal and Child Health Care Hospital, Fengtai District Maternal and Child Health Care Hospital, Fangshan District Maternal and Child Health Care Hospital, and Changping District Maternal and Child Health Care Hospital. Two district-level hospitals in Wuhan are involved as the sub-centers in Wuhan, namely Wuhan Qingshan District Maternal and Child Health Hospital and Wuhan East Lake New Technology Development Zone Fozu Mountain Community Health Service Center. Each sub-center will select communities within the district that are targeted to recruit elderly female patients who are ≥60 years of age with mild to moderate UI by distributing a research subject leaflet. Eligible women need to sign informed consent before being enrolled in the cohorts. Figure 1 illustrates the flow diagram of the study for all subjects.

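### The stated minimum of 188–282 participants carries required progress events forward as if they were women, which implies a 100% progress rate

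*Protocol article*

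**What the plan says.** Section 2.9 of the protocol article builds its sample size in four steps.

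- The rule is in events: for each risk factor in the model, "10 to 15 positive events (UI progress) are be required".
- The rule is applied to "about 10 meaningful risk factors, so 100–150 cases need to be included in the study to get enough statistical power".
- Two allowances follow: "15–20% of the patients were lost in follow-ups", and "the number of participants in the training and validation groups are at a ratio of 2:1".
- The result is a count of women: "at least 188–282 participants in total are required in order to have statistical power".

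The section then explains that more women than expected were willing to join, so that "we planned to recruit 800 participants at most in order to get greater power for the study". Section 2.1 gives the same total as the recruitment plan: "A total of 800 patients will be recruited, 400 from Beijing and 400 from Wuhan".

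**The concern.** The unit changes part-way through. Ten to 15 events per factor times 10 factors is 100–150 events. The article calls this number cases to be included and carries it forward as participants. Turning a required number of events into a required number of women means dividing by the proportion expected to have the event, and no step does so.

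Section 2.10 specifies a Cox model, in which the information comes from events and not from the number enrolled. Section 2.9 is the article's only justification of size. If its minimum is wrong, a reader cannot tell whether the planned 800 sits comfortably above the true requirement or below it.

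**Working it through.** **Inputs**

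- Events per factor: 10 to 15 (section 2.9).
- Factors: about 10 (section 2.9), so E = 100 to 150 events.
- Loss to follow-up: d = 15–20% (section 2.9).
- Training to validation 2:1 (section 2.9), so the total is 1.5 times the training set.
- Planned total: at most 800 (section 2.9).
- 18-month progress rate among followed women, p: not given in the article. The values below are illustrative assumptions.

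**Reproducing the stated figure**

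N = E × 1.5 / (1 − d), with d = 0.20:

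- 100 × 1.5 / 0.80 = 187.5, rounded up to 188
- 150 × 1.5 / 0.80 = 281.25, rounded up to 282

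Both ends match. Other readings do not: d = 0.15 gives 177 and 265, and multiplying by 1.2 instead of dividing by 0.8 gives 180 and 270. The formula contains no p, which is the same as p = 1.

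**What 188–282 women deliver**

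Followed women in the training set = N × 0.80 × 2/3:

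- 188 × 0.80 × 2/3 = 100.3
- 282 × 0.80 × 2/3 = 150.4

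To obtain 100 events from 100.3 women, or 150 from 150.4, p must be 99.7% (94% if loss is 15%). At smaller rates, with 10 factors:

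| Assumed p | Training events, N = 188 / 282 | Events per factor |
|---|---|---|
| 20% | 20 / 30 | 2.0 / 3.0 |
| 30% | 30 / 45 | 3.0 / 4.5 |
| 50% | 50 / 75 | 5.0 / 7.5 |

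Ignoring the split and counting events in the whole cohort does not rescue the figure: 100 / (188 × 0.80) and 150 / (282 × 0.80) both equal 66.5%, and 62.6% at 15% loss.

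**Requirement once p is included**

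N = E × 1.5 / ((1 − d) × p). With d = 0.20 this is 187.5/p to 281.25/p, rounded up:

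| Assumed p | N for 100–150 events, 20% loss | Same, 15% loss |
|---|---|---|
| 20% | 938–1,407 | 883–1,324 |
| 30% | 625–938 | 589–883 |
| 40% | 469–704 | 442–662 |
| 50% | 375–563 | 353–530 |

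**What the planned 800 delivers**

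- At 20% loss: 800 × 0.80 × 2/3 = 426.7 followed women in training. Ten events per factor needs p ≥ 100/426.7 = 23.4%; fifteen needs p ≥ 150/426.7 = 35.2%.
- At 15% loss: 800 × 0.85 × 2/3 = 453.3. The thresholds are 22.1% and 33.1%.
- At p = 20% and 20% loss: 426.7 × 0.20 = 85 events, or 8.5 per factor, below the article's own lower bound.

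**The case against.** The strongest reply is that 188–282 is a floor the study does not use. The plan is for 800 women, 2.8 to 4.3 times that floor (800/282 and 800/188), and 800 satisfies the lower target at any progress rate above about 23%. The endpoint in section 2.7 is also broad: any rise in OABSS counts as progress in the UUI group, and any SUI or UUI criterion counts in the MUI group. The rate could well be high enough. Nothing here shows that the planned study is too small, and 8.5 events per factor at p = 20% is a modest shortfall.

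Much of this stands. The adequacy of 800 can be neither shown nor refuted from the article, and a condensed article may leave a sourced rate to the full protocol. But the article does not leave the calculation out. It publishes one, with a stated minimum that fails its own rule. The 800 is an upper limit, explained by women's willingness to join and presented as extra power above that floor, so it inherits the error.

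The choice of 20% loss is not one-sided in any way that matters. It is the value that reproduces the article's own figures, and 15% moves the thresholds for 800 by only one to two percentage points. Treating lost women as contributing no events is a simplification: follow-up ends at progress (section 2.6), so women who progress early are not exposed to later loss. The article's own inflation for loss makes the same simplification.

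**Conclusion.** The point holds. The 188–282 figure equates progress events with participants and is correct only if essentially all followed women progress. The article itself does not expect that: section 2.6 provides for women without aggravation to be followed through to 18 months. The true requirement is larger by a factor of 1/p, which is about 3.3 times at p = 30% and 5 times at p = 20%.

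The conclusion that the minimum is wrong needs no assumed rate. The size of the error does, and it also rests on 20% loss, no events from lost women, 10 factors, and the 100–150 events being required in the training set, as the article's own 1.5 multiplier implies. Whether 800 suffices remains open: it depends on whether p exceeds about 22–23% for 10 events per factor, or about 33–35% for 15.

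**What to change.** In section 2.9, replace the 188–282 sentence with a calculation that keeps events and women apart:

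- State that 100–150 progress events are needed in the training set.
- Give N = events × 1.5 / (0.8 × p), with an assumed 18-month progress rate p, its source if there is one, and a range. If no sourced rate exists, say so and show the range.
- State what 800 women deliver at 20% loss: at least 10 events per factor if p is about 23% or more, and at least 15 if p is about 35% or more. Give the 15%-loss equivalents (about 22% and 33%) alongside.
- Drop the claim that 188–282 participants are sufficient.

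The cost is a rewrite of one paragraph and a less favourable stated requirement. Recruitment, follow-up and endpoint are unchanged.

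A useful addition would be to limit the number of model parameters to what the observed training events support. That touches the selection procedure in section 2.10, so it goes beyond rewording section 2.9; the correction above stands without it.

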### 2.10. Statistical Analysis and Progress Prediction Model Construction

Data analysis will be done using SAS^®^ 9.3 software (software installation point authorization number: 11202165).

We set up a prediction model based on the Cox regression model. According to univariate Cox regression analysis, risk factors with a *p* value < 0.05 will be selected to enter the model predictive factors, and then the forward method will be used to carry out multi-factor Cox regression analysis to build the prediction model of the UI disease progress, predicting the risk of UI disease progress. The subjects will be randomly divided into training and validation cohorts according to the ratio of 2:1. The discriminative ability of the prediction model will be analyzed through the area under the ROC curve, and the accuracy of the model will be evaluated by the Hosmer–Lemeshow decile chi-square test. The calibration of the ten models will be assessed with the predicted versus observed probability plots, and the discrimination of the models will be assessed with the prognostic separation D-statistic (D-statistic). The bootstrap method will be used to further internally verify the discriminative ability and accuracy of the model. External validation uses different hospitals for spatial validation to evaluate the extrapolation of the model. Moreover, 100 bootstrap random samplings will be performed to generate 100 bootstrap test sets. For each test set, the area under the ROC curve method and Hosmer–Lemeshow deciles will be used in the square test to objectively evaluate the stability and variation range of the model’s discriminative ability and accuracy. 

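### Univariable p<0.05 screening plus forward selection over about 58 candidates will overfit, and neither the sizing in section 2.9 nor the bootstrap as described in section 2.10 accounts for it

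*Protocol article*

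**What the plan says.** Section 2.10 builds the model in two steps. Factors with a univariable Cox p "value < 0.05 will be selected to enter the model predictive factors"; "then the forward method will be used to carry out multi-factor Cox regression analysis to build the prediction model". No entry threshold for the forward step, shrinkage or penalisation is given.

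Section 2.9 sizes the study per risk factor: "10 to 15 positive events (UI progress) are be required" for each, and "It is preliminarily estimated that there are about 10 meaningful risk factors". Adding loss ("15–20% of the patients were lost in follow-ups") and a 2:1 split, it concludes that "at least 188–282 participants in total are required in order to have statistical power", and then plans up to 800.

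For validation, section 2.10 lists four things: a random split ("The subjects will be randomly divided into training and validation cohorts according to the ratio of 2:1"), described after the model-building steps; plots of predicted against observed risk; spatial validation across hospitals; and a bootstrap for internal verification. The bootstrap detail is that "100 bootstrap random samplings will be performed to generate 100 bootstrap test sets", with AUC and Hosmer–Lemeshow computed on each to show how stable and variable performance is.

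**The concern.** An events-per-factor rule protects against overfitting only if it counts every candidate the data are allowed to choose from. Section 2.9 counts the factors expected to remain at the end. Filtering at p<0.05 and then selecting forward tends to keep candidates whose effects look large by chance. It passes on their inflated coefficients unshrunk and misses some real predictors.

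The Discussion plans to put the model into a mobile app that gives risk predictions to patients and clinicians. Overfitted coefficients would make those risks too extreme: too high for women at the upper end and too low at the lower end. A bootstrap that only re-scores the finished model on resampled development data would not show this.

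**Working it through.** **1. The plan's own figure.** Events ÷ (1 − loss) × 3/2, at 20% loss:
- 100 ÷ 0.80 × 1.5 = 187.5, rounded up to 188
- 150 ÷ 0.80 × 1.5 = 281.25, rounded up to 282

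The stated range is reproduced. The 100–150 comes from 10 factors × 10–15.

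**2. Candidates.** Counting each item once:
- Table 2: 15 (age to smoking) + 4 comorbidities + 5 (pelvic inflammatory disease to family history) + 5 incontinence-history items + 4 (POP-Q, Oxford grade, pad test, severity) + 3 questionnaire scores = 36.
- Section 2.6: electrophysiology 6 + uroflowmetry 4 + ultrasound 9 + morphology 2–3 = 21–22.
- Total: 57–58. Categorical items would need more than one parameter each.

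**3. The plan's rule applied to candidates.** 58 × 10 = 580 and 58 × 15 = 870 events. Training at 800 recruited holds 800 × 0.80 × 2/3 ≈ 427 women (453 at 15% loss), so 580 events cannot be reached at any progression rate.

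**4. Events available.** The article gives no progression rate, so 10–50% is assumed:
- 10%: 43 events, 43/58 = 0.7 per candidate
- 30%: 128 events, 128/58 = 2.2
- 50%: 213 events, 213/58 = 3.7

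**5. Chance entries at the screen.** If all 58 are null, 58 × 0.05 = 2.9 are expected to pass, and P(at least one) = 1 − 0.95^58 = 0.95. If 10 are real, 48 × 0.05 = 2.4.

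**6. Simulation.** 640 women analysed, 427 in training, 58 independent normal candidates, 10 real at log-HR 0.2 per SD, visits at 6, 12 and 18 months. Univariable p<0.05 was followed by forward selection at p<0.05, with 60 simulated studies per row. The effect size, independence and forward threshold are assumptions. All selection was done in the training cohort.

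| Progression | Apparent AUC | Fixed model re-scored on training resamples | Split validation | True AUC | Bootstrap repeating selection | Calibration slope |
|---|---|---|---|---|---|---|
| 15% | 0.717 | 0.718 | 0.587 | 0.586 | 0.612 | 0.39 |
| 30% | 0.701 | 0.701 | 0.613 | 0.620 | 0.618 | 0.59 |
| 50% | 0.725 | 0.725 | 0.663 | 0.659 | 0.661 | 0.71 |

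- Optimism (apparent minus true) is 0.131, 0.081 and 0.066.
- Re-scoring the fixed model on training resamples removes none of it. Re-scoring on validation resamples gives 0.588, 0.612 and 0.663, close to the truth. The article does not say which data the resamples come from.
- Repeating the selection (20 resamples per study) removes nearly all the optimism at 30% and 50%, and most of it at 15%.
- With no real factors at 30% progression, apparent AUC is 0.592 against a true 0.501.
- Near the stated minimum (282 × 0.80 ≈ 225 analysed, 150 in training, 30%), apparent AUC is 0.705, true 0.556, slope 0.26.
- The SD of the split-validation AUC is 0.04–0.07 with 640 analysed.
- A few refits did not converge.

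**The case against.** A reader might infer that the optimism is never removed and that internal validation would simply confirm the inflated model. The article does not support that. It also plans a 2:1 validation cohort, spatial validation and calibration plots. When selection is confined to training, the held-out AUC is honest: 0.587 against a true 0.586, 0.613 against 0.620, and 0.663 against 0.659. The overfitting would then be exposed.

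A reader might also take it as fact that the bootstrap never rebuilds the model. That is the natural reading of resamples called test sets, but the text is silent. The separate general sentence on bootstrap verification could mean a conventional procedure with refitting, and a condensed article may leave such detail to a fuller plan.

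Both objections stand as limits on the claim. They do not remove it:
- The two-step selection without shrinkage and the sizing on final factors are stated, not omitted.
- Validation measures overfitting but leaves the coefficients unchanged.
- The split is described after model building, and nothing confines screening and forward selection to the training cohort. If they use all women, the random validation cohort is contaminated.
- A single split gives an imprecise estimate.

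**Conclusion.** The point holds in this form. The selection procedure will overfit, section 2.9 counts expected survivors instead of candidates, and the bootstrap as described states no correction for optimism. With 800 recruited, the simulated optimism is about 0.07–0.13 in AUC, and the calibration slope of 0.39–0.71 is well short of 1.

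The sizes rest on assumptions that are not in the article: the progression rate, 10 true factors at log-HR 0.2 per SD, independent candidates, and a forward threshold of 0.05. Correlated or multi-category candidates would change the size, not the direction. The bootstrap part depends on its being a re-scoring of a fixed model on development data. The plan should be changed on this point before the model is built; the study's data collection is not affected.

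**What to change.** In section 2.10:
- Replace the p<0.05 filter and forward steps with a penalised Cox model (for example LASSO, elastic net or ridge, tuned by cross-validation) over a pre-listed candidate set.
- In each bootstrap sample, repeat the whole selection and fitting procedure, test the result on the original data, and subtract the mean optimism from discrimination and calibration slope.
- If the 2:1 split is kept, confine all screening, selection and tuning to the training cohort.

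In section 2.9, state events per candidate parameter, with the assumed progression rate, instead of per expected final factor.

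Penalisation was not simulated at 427 women in training. A separate run of 25 simulated studies with ridge Cox on 800 women gave slopes of 1.24 and 0.98 at its two effect sizes. It can therefore over-shrink, and the slope should still be reported. LASSO and elastic net were not tested.

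The cost is wording and computing time, with no new data. Penalised coefficients have no simple p-values, and the reported AUC will be lower.

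### With a random 2:1 split of one pool and no outside hospital described, the planned spatial validation is external only if its hospitals are defined; the random hold-out adds little beyond the bootstrap

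*Protocol article*

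**What the plan says.** Section 2.1 defines one pool: "A total of 800 patients will be recruited, 400 from Beijing and 400 from Wuhan". Recruitment runs through sub-centres: "Four district-level hospitals in Beijing are involved as the sub-centers in Beijing", and "Two district-level hospitals in Wuhan are involved as the sub-centers in Wuhan". No other hospital appears as a source of data.

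Section 2.10 then lists three kinds of validation:
- A random split: "The subjects will be randomly divided into training and validation cohorts according to the ratio of 2:1". It is not restricted or stratified by hospital or city.
- A bootstrap: "The bootstrap method will be used to further internally verify the discriminative ability and accuracy of the model", with the further statement that "100 bootstrap random samplings will be performed to generate 100 bootstrap test sets".
- A spatial test: "External validation uses different hospitals for spatial validation to evaluate the extrapolation of the model". The hospitals are not named, and the text does not say which fitted model they test.

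Section 2.9 builds the 2:1 ratio into the sample size. The Discussion calls the model primary and leaves its wider application to a later large-scale study.

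**The concern.** A spatial validation is informative when the hospitals that test the model had no part in fitting it. A random split of individual women does the opposite: it makes training and validation cohorts alike in hospital, city, examiner and case mix. If a predictor behaves differently in Beijing and Wuhan, the training set has already averaged over that difference, and the validation set has the same mixture. Good performance there says nothing about a hospital the model has not seen.

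At stake is the claim about extrapolation in 2.10, for a model that the Discussion intends to turn into an app. A second, smaller matter is efficiency. The random hold-out is another internal validation beside a bootstrap that does the same job, and it takes a third of the women out of model development.

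**Working it through.** **Step 1. The plan's own sample size.** Inputs from 2.9: "10 to 15 positive events (UI progress) are be required" per risk factor, about 10 factors, 15–20% loss, ratio 2:1. Formula: N = (events per factor × 10) × 3/2 ÷ (1 − loss).
- Lower: 100 × 1.5 / 0.80 = 187.5, so 188.
- Upper: 150 × 1.5 / 0.80 = 281.25, so 282.

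This reproduces the stated 188–282 at 20% loss (15% would give 177–265). The arithmetic is sound, and the hold-out is a deliberate, budgeted choice.

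**Step 2. Is any study hospital absent from training?** If each woman has probability 2/3 of being in training, a hospital with n women has none there with probability (1/3)^n. Equal recruitment within each city is my assumption.
- Beijing sub-centre: 400/4 = 100 women, about 67 in training; (1/3)^100 ≈ 2 × 10^-48.
- Wuhan sub-centre: 400/2 = 200 women, about 133 in training; (1/3)^200 ≈ 4 × 10^-96.
- Even with 13 women: (1/3)^13 ≈ 6 × 10^-7.

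So each recruiting hospital is in the training set for practical purposes, whatever the exact shares.

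**Step 3. What the hold-out costs.** Of 800 women, about 533 train and 267 validate.
- 20% loss: 640 evaluable, about 427 training and 213 validation.
- 15% loss: 680 evaluable, about 453 training and 227 validation.

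The article gives no progression rate, so a range is assumed. Events at 20% loss = 640 × rate for all women, and two thirds of that for training:
- 10%: 64 in all, 43 in training
- 20%: 128 in all, 85 in training
- 30%: 192 in all, 128 in training
- 40%: 256 in all, 171 in training

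Against the plan's lower target of 100 events, all women suffice from a rate of 100/640 = 15.6%, and the training set from 100/426.7 = 23.4%. Between these rates the split alone takes development below the target. At 20%, events per factor fall from 12.8 to 8.5.

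**Step 4. How far a random split could mislead.** This depends on how much predictor effects differ between cities, which the article does not give. Simulated studies (10 predictors, 640 evaluable women, about 30% to one third progressing, 150 runs per setting) gave these mean C-statistics for random split / train in one city and test in the other / a new city:
- SD of city-specific log hazard ratios 0: 0.66 / 0.66 / 0.67
- SD 0.05: 0.656 / 0.647 / 0.658
- SD 0.10: 0.658 / 0.635 / 0.647
- SD 0.15: 0.67 / 0.63 / 0.64
- SD 0.25: 0.70 / 0.59 / 0.62

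The 0.05 and 0.10 rows come from a separate run with equal effects across predictors, so small differences between rows should not be read closely. Scoring only the held-out Wuhan women with the random-split model gave 0.67 and 0.69 at SD 0.15 and 0.25, so testing one study city after a random split does not reveal the loss.

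**The case against.** The strongest reply is that 2.10 lists the spatial test as a separate step and never says it reuses the randomly split model. The hospitals in question could be outside the study, or whole hospitals held out and the model refitted, and a condensed article may leave such detail to a fuller document. This stands. A reader might infer that the external validation is certainly not external, but the text does not go that far. What can be said is conditional: for the one split that is described, no study hospital is new to the model, and neither alternative is described.

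A reader might also infer that the reason for recruiting in two cities collapses with this test. It does not. The Discussion gives representation of northern and southern patients as the reason, and pooling both cities serves that.

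Nor is the split an error. It is conventional, it is budgeted, and 800 is about 2.8 times the upper minimum (800/282). If 30% progress, the 128 training events lie inside the plan's 100–150 target.

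Finally, the simulated gaps come from their inputs. They vanish at SD 0 to 0.05. At SD 0.10 the random split is 0.011 too high and the by-city estimate 0.012 too low. If typical log hazard ratios are near 0.20, an SD of 0.15–0.25 is 75–125% of the effect itself, which is large. These figures show a direction under assumed heterogeneity and do not measure a bias in this study.

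**Conclusion.** The point holds in conditional form. With the pool and split as described, every Beijing and Wuhan hospital contributes to training, so a spatial test of that model on study hospitals is not external and cannot show transportability. It would be external only with hospitals outside the pool, or with whole hospitals held out and the model refitted, and the article describes neither.

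The hold-out is a separate inefficiency: about 213 of 640 evaluable women at 20% loss are kept out of development for a check that the bootstrap largely covers. Whether this takes events below the plan's own target depends on the unstated progression rate. Any optimism in the C-statistic depends on unknown between-city heterogeneity and is negligible if that is small. This is a worthwhile, inexpensive improvement to the validation design. It does not invalidate the study.

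**What to change.** In 2.10:
- Replace the random 2:1 split with internal–external cross-validation, either by city (fit in one, test in the other, then reverse) or by leaving out one hospital at a time. Repeat the whole procedure in each fit, including the univariate screen and forward selection. Report discrimination and calibration for each held-out unit.
- Develop the final model on all women, and use the bootstrap, again repeating selection, to correct its optimism.
- Call the result geographic internal–external validation. Keep the word external only if hospitals outside the development data are named and tested with the final model.

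Leave the minimum in 2.9 as it is. Removing the factor 1.5 would give 100/0.8 = 125 to 150/0.8 = 188, which lowers a figure that already treats required events as required participants. If the mention of the ratio is reworded for consistency, the number should stay.

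The cost is wording and extra analysis, with no new data. The downside is that held-out fits use less data. At 20% loss a by-city fit uses 400 × 0.8 = 320 women, so its results are somewhat pessimistic, and two cities give only two folds. Leaving out one hospital keeps more for fitting (700 × 0.8 = 560 or 600 × 0.8 = 480 with equal shares), but a held-out Beijing sub-centre would have only 100 × 0.8 × 0.2 = 16 events at an assumed 20% rate, so hospital-level results will be imprecise.

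### Only 100 bootstrap samples are planned to describe the variation range of model performance, which leaves avoidable simulation error in that range

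*Protocol article*

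**What the plan says.** Section 2.10 of the protocol article describes a Cox prediction model with several layers of validation: a 2:1 split into training and validation cohorts, AUC, the Hosmer–Lemeshow test, calibration plots, the D-statistic, internal verification by bootstrap, and spatial validation across hospitals. It then adds that "100 bootstrap random samplings will be performed to generate 100 bootstrap test sets". On what is computed in each, it says: "For each test set, the area under the ROC curve method and Hosmer–Lemeshow deciles will be used". The stated purpose is to "objectively evaluate the stability and variation range of the model’s discriminative ability and accuracy".

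The section gives no reason for 100, and no larger number of resamples appears elsewhere in the article. It does not say whether the range is a percentile range, a minimum-to-maximum range or one based on a standard deviation.

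**The concern.** The number of resamples that suffices depends on what is read from them. One hundred is adequate for an average: the mean AUC over 100 resamples has a simulation error of only 1/√100 = 0.1 of the AUC's standard error. A range is more demanding. With 100 resamples, each end of a 95% range rests on the two or three most extreme values, so a second run on the same data with another random seed could give visibly different limits. What is at stake is the reproducibility of the spread reported for discrimination and calibration. The point estimates, the choice of predictors and any decision about the model are not affected.

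**Working it through.** **The plan's figure.** The 100 is a chosen constant, so there is nothing to reproduce. The check is how much simulation error it leaves.

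**Inputs from the article**
- Number of resamples B = 100 (section 2.10).
- Maximum recruitment 800 (section 2.9).
- Split: "The subjects will be randomly divided into training and validation cohorts according to the ratio of 2:1" (section 2.10), so the validation set is about 800/3 ≈ 267.
- Software SAS 9.3 (section 2.10).
- Loss to follow-up 15–20% (section 2.9).

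**Assumptions, because the article gives no figures:** AUC 0.65 to 0.75; progression in 15% to 40% of women; an approximately normal bootstrap distribution of the AUC; progression treated as yes/no for the AUC's standard error.

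**Step 1: simulation error of a 95% percentile limit.** In units of the AUC's standard error it is √(p(1 − p)/B)/φ(z), with p = 0.025 and z = 1.96.
- B = 100: √(0.025 × 0.975/100)/φ(1.96) = 0.267
- B = 1000: 0.084
- B = 2000: 0.060

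Simulation agrees: 0.24 to 0.27 at B = 100, depending on the percentile rule, and 0.083 to 0.084 at B = 1000. The ratio of 100 to 1000 is √10 ≈ 3.2.

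**Step 2: translation to the AUC scale.** The Hanley–McNeil standard error is √{[A(1 − A) + (n₁ − 1)(q₁ − A²) + (n₀ − 1)(q₂ − A²)]/(n₁n₀)}, with q₁ = A/(2 − A) and q₂ = 2A²/(1 + A).

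Worked case: 267 women, 15% progressing, A = 0.65. Then n₁ = 40, n₀ = 227, q₁ = 0.4815, q₂ = 0.5121 and A² = 0.4225. The numerator is 0.2275 + 39 × 0.0590 + 226 × 0.0896 ≈ 22.78. Dividing by 40 × 227 = 9080 and taking the root gives 0.050.

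| Women resampled | AUC standard error over the assumed range | Simulation error of one limit at B = 100 (× 0.25) |
|---|---|---|
| 267 (validation set) | 0.032–0.050 | 0.008–0.013 |
| 800 (all) | 0.018–0.029 | 0.005–0.007 |

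If 20% are lost, 213 and 640 women remain, and the last column becomes 0.009–0.014 and 0.005–0.008.

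**Step 3: realised content of a nominal 95% range.** With the SAS default percentile rule, the central 95% of runs contain between 88.7% and 97.7% of the bootstrap distribution at B = 100. At B = 1000 the spread is 93.4% to 96.2%.

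**Step 4: other readings of the range**
- Standard deviation: the relative simulation error is 1/√(2(B − 1)), which is 7.1% at B = 100 and 2.2% at B = 1000.
- Minimum to maximum: the mean width is 5.0 standard errors at B = 100 and 6.5 at B = 1000. It grows with B, so more resamples do not make it settle.

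**Step 5: is there a bias in width?** The true 95% width is 3.92 standard errors. At B = 100 the mean departure from it depends on the rule:

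| Rule | Mean width (standard errors) | Departure from 3.92 |
|---|---|---|
| SAS default | 3.89 | −0.7% |
| Linear interpolation | 3.75 | −4.2% |
| (B + 1)p | 4.08 | +4.2% |

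The sign is not fixed by anything in the article.

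**The case against.** The strongest reply is that section 2.10 commits only to a variation range. It names no 95% level, percentiles or confidence interval. This is a condensed article, and the interval type, percentile rule and seed may properly stand in a fuller document. That is right, and their absence is not held against the plan. The number 100 is stated, however, and both natural summaries of spread (a percentile range or a standard deviation) are noisier than they need be at that number.

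A second reply is that the effect is small: about a quarter of the AUC's own sampling error in each limit, with no threshold or success criterion depending on it. The resamples are also one layer among several forms of validation. This stands, and it is why the point is only a possible improvement.

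A third reply is that the figures rest on normal theory, while the Hosmer–Lemeshow chi-square is not normal. This also stands. Its tail limits are noisy at 100 resamples for the same reason, but the sizes above apply to the AUC only.

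A reader might infer more: that 100 resamples make the reported range too narrow on average. The article does not support that. Under the default rule of the software it names, the mean loss of width is under 1%; another rule gives a range that is slightly too wide, and minimum to maximum is wider still.

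**Conclusion.** The point holds as a minor gain in precision. With 100 resamples, each limit of a 95% percentile range for the AUC carries simulation error of about a quarter of the AUC's standard error: about 0.005 to 0.013 for 267 to 800 women, given an assumed AUC of 0.65 to 0.75 and 15% to 40% progression. A reported standard deviation would carry about 7%. The error is random and removable. No systematic bias in width is claimed, and no size is given for the Hosmer–Lemeshow results.

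It would also be wrong to read this as a flaw in the model building. Whether the modelling steps are repeated in each resample concerns optimism, which is a separate matter from the number of resamples.

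**What to change.** In the bootstrap sentence of section 2.10, replace both instances of 100 with at least 1000, and state that the variation range is the 2.5th to 97.5th percentile of the resampled values rather than minimum to maximum. The second change is needed because a minimum-to-maximum range only widens as resamples are added. Together they cut the simulation error of each limit about threefold, from about 0.25 to about 0.08 of the AUC's standard error. The cost is computing time for at most 800 participants; recruitment, data collection and the rest of the analysis are unchanged.
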